***8.3 Data analysis***

For the three sets of qualitative interview data separate Framework analyses will be undertaken with the support of QSR NVivo (version 10) data management and analysis software. This method permits identification and cross-classification of variables directly from digital transcriptions. The analysis process consists of identifying key concepts and themes and mapping their range and diversity, followed by a process of interpretation where patterns of association are investigated and possible reasons for these explored. In achieving this all transcripts will be summarised, charted and coded for recurrent themes. Specific analytic intentions are associated with each of the three interview data sets:

*Residents/family carer interviews*: the framework will be developed to explore the elements of perceived impact and acceptability of TPTNS as a therapeutic intervention, by residents and family carers, in both the short-term and for the longer-term.

*CH staff:* The focus group and individual interview framework will highlight the experience of CH staff in developing their new skills set and the facilitators and challenges they experienced implementing them into routine practice. The elements of the COM-B model which formed the theoretical underpinning of the staff interview schedule will be key concepts in this framework.

*CH managers:* The focus of the framework for analysing the CH managers’ interviews will be the cultural, economic, strategic and quality impacts associated with participating in the trial and implications for implementation and sustainability at the organisational level.

The coherence, transparency and validity of the interpretations from these three different framework analyses will be assessed through regular iterative discussion between the RA with qualitative research experience and the study team members with qualitative expertise.

## 9. SAMPLE SIZE AND PROPOSED RECRUITMENT RATE

**9.1 Sample size**

A total of 500 residents will be required for this study, recruited across the two regions in accordance with allocation of RRA resources in that region. The worthwhile difference we believe the intervention will result in is a reduction of 200ml/24 hours. There is a lack of data available on the potential standard deviation of Pad Weight Tests37 (PWT) in CH residents; however, a small RCT2 reported results on this outcome. The SD from the trial was about 450ml, but given the small and selected sample included we estimated the upper 95% confidence interval around the SD which was approximately 570ml/24 hours, hence the standardised effect size of 0.35 (i.e. 200/570). To detect that difference with 90% power at the two-sided 5% alpha level we need primary outcome data on 344 participants. The limited data available suggested that the intra-class correlation (ICC) for any possible clustering effect was likely to be negligible; however, we have inflated this number to 500 to cover a conservative estimate of attrition to the primary outcome of about 30% due to death of CH residents and potential transfers to other CHs.

**9.2 Recruitment rates**

Large CHs with 100 or more residents and smaller CHs with a minimum of 25 residents will take part. The minimum population of residents will be 1700, although the expected number will be considerably higher. Approximately 70% will have UI and 10% will be in receipt of palliative care or do not use the toilet/toilet aid for elimination, thus there will be an estimated minimum total pool of 1071 eligible residents from whom we will recruit 500. Assuming similar recruitment rates to the HTA funded DCM-EPIC study undertaken in CHs of 60% of eligible CH residents, we would have at least 643 residents from whom to recruit our sample of 500. Recruitment will be undertaken over an 18-month period, commencing month 6 and will be completed by month 24. At least four new CH sites will be established every 3 months during the recruitment period, depending on CH size and location.

All trial and process evaluation data will be collected by month 30 (see Gantt chart: Figure 1).

## 10. STATISTICAL ANALYSIS

All analyses will be undertaken according to a previously agreed statistical analysis plan (SAP) and based on the intention-to-treat principle. The SAP will be agreed with the TSC, including the independent statistician, before any data analysis commences.

**10.1 Main effectiveness analysis:**

All baseline characteristics, follow-up measurements and safety data will be described using the appropriate descriptive summary measures: mean and SD for continuous and count outcomes or medians and inter-quartile range if required for skewed data, numbers and percentages for dichotomous or categorical outcomes.

The primary outcome, measured at 6 weeks post randomisation, will be analysed using linear regression correcting for baseline 24- hours PWT and other prognostic variables; all models will include a random effect for CH. The statistical analysis of the primary outcome will be by intention-to-treat (ITT); we will explore effects of compliance with treatment using causal models.  Potentially missing data will be handled using appropriate methods depending on the amount and pattern of missingness with sensitivity analysis to test assumptions.

Secondary outcomes will be analysed using a similar strategy employing generalised linear models suitable for the outcome. All treatment effects will be derived from these models and presented with 95% confidence intervals. All analysis will be performed and reported in accordance with the CONSORT statement and the ICH E9 ‘Statistical Principles in Clinical Trials’.

A single main analysis will be performed at the end of the trial when the 18 week follow up has been completed. An independent Data Monitoring and Ethics Committee will review confidential interim analyses of accumulating data, at its discretion but, at least annually.

**10.2 Planned subgroup analyses:**

Subgroup analyses will be carried out accordingly by:

- Gender
- UI severity
- Dependency in toilet use
- Cognitive status
- Falls status

Stricter levels of statistical significance (2P<0.01) will be sought, reflecting the exploratory nature of these analyses. Heterogeneity of treatment effects amongst subgroups will be tested for using the appropriate subgroup by treatment group interactions.

10.3 Process evaluation data analysis

Process evaluation data analysis will address the adherence to the stimulation programme by group, at time point 1 (6-weeks post-randomisation), the end of the stimulation programme. Characteristics of residents, and the stimulation programme they received will be described using appropriate summary measures and the proportion who received the therapeutic minimum > 8 stimulation sessions and the full 12 session programme presented. Overall fidelity to the allocated group will also be assessed and presented to illuminate resident elements of the outcome analysis including: total stimulation time, mean intensity of stimulation and accuracy of electrode position. Stimulation diaries will be analysed to identify data to inform our understanding of when, how and who delivers the electrical stimulation in practice.

11. ECONOMIC EVALUATION

The economic evaluation will compare the costs and outcomes of TPTNS compared with usual continence care pathways and present these in a cost consequence analysis.

**11.1 Collection of resources use and data**

Staff time required for training and the delivery of the intervention will be recorded by each CH, including the number of hours and the staff grade. This will be costed using the appropriate pay scales for each site. The costs of the trainer and the materials (TPTNS machines, TPTNS handbook and training DVD) will be based on the market rates for these items. A resource use questionnaire (RUQ) will be developed on which the RRA will record at baseline the usual continence care pathway including details on usage of pads and other equipment, medication which may affect continence level, and (if appropriate) number of staff required to assist resident to use the toilet. At the follow up time points, in combination with the 24-hour bladder diary, the RRA will use this questionnaire to update the continence care pathway. If residents have required any care from health professionals external to the CH as a result of their UI, this will also be recorded on the resource use questionnaire. Unit costs will be attached to the resources required using standard sources (including NHS Reference Costs, Unit Costs of Health and Social Care and British National Formulary65-67.

**11.2 Quality of Life**

Participant quality of life data is being collected as described in Section 6 on Outcomes.

**11.3 Analysis**

A cost consequence analysis presents the costs and outcomes in a disaggregated form (often called a ‘balance sheet’ approach). This approach is appropriate as there is more than one multidimensional outcome of importance which may not be captured via a Cost Effectiveness Analysis using the clinical primary outcome. It is possible to calculate utility values using the DEMQOL and DEMQOL–Proxy data. If the analysis of this data demonstrates a difference in QOL between the intervention and control arms, we will seek to calculate the utility values using the DEMQOL-U and calculate QALYs which could be used in a Cost Utility Analysis.

##

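### Section 11.3 calculates utilities and QALYs only if a quality-of-life difference is found, so the existence of the optional cost-utility analysis depends on its own result

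*Protocol*

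**What the plan says.** Section 11 of the protocol sets the main economic analysis: costs and outcomes are compared, and the team will "present these in a cost consequence analysis". No result has to be seen first. Section 11.3 then adds a conditional step, introduced by "If the analysis of this data demonstrates a difference in QOL between the intervention and control arms". In that event, "we will seek to calculate the utility values using the DEMQOL-U and calculate QALYs which could be used in a Cost Utility Analysis". The section does not say whether the resident or the proxy measure decides, at which time point, by what test, or what counts as a demonstrated difference.

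DEMQOL and DEMQOL-Proxy are scheduled at baseline, 6 and 18 weeks (Table 1) and are secondary outcomes at 6 and 18 weeks (Section 5.2). The sample size in Section 9.1 rests on the 24-hour pad weight test alone: "To detect that difference with 90% power at the two-sided 5% alpha level we need primary outcome data on 344 participants". No quality-of-life effect, SD or power appears anywhere in the protocol.

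**The concern.** The rule lets an observed result decide whether an analysis is done at all. Three things are wrong with that.

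- Cost-utility analysis needs an estimate of the cost difference and the QALY difference with their joint uncertainty. A small or imprecise QALY difference is a usable result, especially if costs differ. Failing to show a difference is not evidence that there is none.
- The quantity tested is not the quantity released. A DEMQOL comparison at 6 or 18 weeks needs a completed questionnaire at that visit. QALYs accumulate utility over time and conventionally count death as zero. Section 4.7 names death as the main expected source of attrition, and Section 9.1 allows for about 30% attrition from deaths and transfers. A null score comparison among responders therefore does not imply a null QALY difference.
- Any threshold on the observed difference favours large estimates. Where QALYs are reported, they come from the trials in which the DEMQOL difference happened to look big.

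At stake is the credibility of any cost-utility result and, where the condition fails, the loss of information that the trial has already collected.

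**Working it through.** **Inputs from Section 9.1:** the target difference "is a reduction of 200ml/24 hours"; the SD is taken as "the upper 95% confidence interval around the SD which was approximately 570ml/24 hours", giving a standardised effect of 0.35; two-sided alpha 5%; power 90%. Allocation is 1:1 (Section 4.5).

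**The plan's own figure.** Per arm, n = 2(1.960 + 1.282)² / 0.35² = 171.6, so 172 per arm and 344 in total, as stated. Dividing by 0.70 for attrition gives 492, close to the stated 500. The sample size is sound for pad weight.

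**Assumptions for the condition,** because the protocol gives none: a demonstrated difference means two-sided p<0.05 on one unadjusted comparison; 344 residents have quality-of-life data; the true effect d lies between 0.10 and 0.35 SD.

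**Formulas.** The standard error in SD units is √(2/172) = 0.1078. The observed difference must exceed 1.96 × 0.1078 = 0.211 SD. With expected z-value λ = d/0.1078, the probability of a significant benefit is P = 1 − Φ(1.96 − λ). The mean z-value given a significant benefit is λ + φ(1.96 − λ)/P. Dividing that by λ gives the overstatement.

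For d = 0.20: λ = 1.855; P = 1 − Φ(0.105) = 0.458; mean z = 1.855 + 0.397/0.458 = 2.72; ratio = 2.72/1.855 = 1.47.

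| True effect (SD) | Probability of significant benefit | Mean estimate given significant benefit (SD) | Overstatement |
|---|---|---|---|
| 0.10 | 15% | 0.267 | ×2.67 |
| 0.15 | 29% | 0.279 | ×1.86 |
| 0.20 | 46% | 0.293 | ×1.47 |
| 0.25 | 64% | 0.313 | ×1.25 |
| 0.30 | 79% | 0.339 | ×1.13 |
| 0.35 | 90% | 0.371 | ×1.06 |

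A significant difference in the wrong direction adds at most 0.2 percentage points over this range. Simulation with 2 million draws at 0.10, 0.20 and 0.35 SD gave the same figures.

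**Fewer responders (assumed).** At d = 0.20, 250 responders give 35% and ×1.67; 172 responders give 26% and ×1.95.

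**No true effect.** One test meets the condition in 5% of trials. The wording does not exclude using any of several comparisons. With two (resident and proxy, or 6 and 18 weeks) the figure is 8 to 10%; with all four it is 13 to 19%. The upper end of each range assumes independence and the lower end a correlation of 0.7.

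**Without the condition** there is no selection, and the ratio is 1.00 at every effect size.

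**The case against.** The strongest defence is that little depends on this clause. The cost consequence analysis is the stated economic objective (Section 2, objective 3; Sections 11 and 11.3) and is presented whatever the result. The cost-utility step is only something the team will seek to do and that QALYs could serve. The DEMQOL comparisons stay visible in any case, because Section 10.1 presents all treatment effects with 95% confidence intervals. All of this stands, and it limits the weight of the point.

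A reader might infer more than the documents support:

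- *That a significance test is specified.* It is not. A p-value is the natural reading, but it is an inference. Selection follows from any threshold on the observed difference; only its size depends on which one.
- *That the reported cost per QALY is biased either way.* If the condition fails, no cost per QALY is reported, so none is biased. If it is met, the estimate is the one an unconditional analysis would have given in that trial. The bias is an average over the trials that report.
- *That QALYs are inflated by a known percentage.* The ratios apply to the DEMQOL score. They pass to DEMQOL-U QALYs only as far as the two are correlated, and that correlation is not given.
- *That the trial is underpowered for quality of life.* It is not sized for it, which is a different statement. At 0.35 SD with full data, power would be 90%.

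The calculation is also unadjusted. Section 10.1 plans a strategy for secondary outcomes similar to the baseline-adjusted primary model, which would raise power and reduce the overstatement. Incomplete questionnaires in a population that includes cognitive impairment would do the opposite.

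None of this justifies the condition itself. The analysis plan is not at hand, but the rule stands in the protocol and is not a detail deferred to it.

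**Conclusion.** The point holds in a limited form. Section 11.3 makes the existence of the optional cost-utility analysis depend on the quality-of-life result, in a trial sized only on pad weight. The size of the resulting selection is uncertain: from about ×2.7 at a true DEMQOL effect of 0.10 SD to about ×1.06 at 0.35 SD. This assumes a two-sided 5% threshold, 344 analysed and one unadjusted comparison. No single value in that range has special standing. The defect is worth correcting because the rule is explicit and easily removed, not because the trial's main conclusions are at risk.

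**What to change.** Delete the condition in Section 11.3. Calculate utilities and QALYs from the DEMQOL data already scheduled, whatever the DEMQOL comparison shows, and report incremental costs and incremental QALYs with their joint uncertainty beside the cost consequence analysis. The technical detail of the QALY calculation can sit in the analysis plan. Alternatively, decide before unblinding that no cost-utility analysis will be done, and say so. Either choice makes the decision independent of the result. The first costs some extra health-economic analysis and needs no new data; the second costs nothing but forgoes the QALY result.

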## 12. ORGANISATION: TRIAL MANAGEMENT AND OVERSIGHT ARRANGEMENTS

The Gantt chart (Figure 1) indicates when anticipated major trial events will occur, including recruitment, analyses and meetings. These time-related milestones will be used to enable close monitoring of progress.

## Figure 1 – ELECTRIC Gantt chart

[figure not shown]

**12.2 Local organisation in CH sites**

The local PI and RRA in each site are responsible for all aspects of local organisation including identifying potential recruits, consenting, completing and maintaining appropriate documentation. The site agreement documents the full list of responsibilities for sites. Appropriate members of the local team are knowledgeable about the Protocol and will have appropriate Good Clinical Practice (GCP) training, if applicable. A trial-specific delegation log is prepared for each site, detailing the responsibilities of each member of staff working on the trial. The local team is also responsible for notifying SAEs to the Trial Office (see section 7).

**12.3 Project Management Group (PMG)**

The trial is supervised by its Project Management Group (PMG). This consists of the grant holders and representatives from the Trial Office and the CHaRT trial team. Observers are invited to attend at the discretion of the PMG. The PMG will meet/teleconference every three months on average, but monthly in the initial set-up stage.

**12.4 Trial Steering Committee (TSC)**

A Trial Steering Committee (TSC), with independent members, oversees the conduct and progress of the trial. The TSC Charter documents the terms of reference of the TSC, the template for reporting and the names and contact details of members of the TSC. This Charter is filed in the Trial Master File (TMF).

**12.5 Data Monitoring Committee (DMC)**

An independent Data Monitoring and Ethics Committee (DMEC) oversee the safety of subjects in the trial. The DMEC Charter documents the terms of reference of the DMEC and the names and contact details and is filed in the TMF. The Committee meets regularly to monitor the trial data and make recommendations as to any modifications that are required to be made to the protocol or the termination of all or part of the trial. CHaRT has adopted the DAMOCLES Charter for DMECs.

## 13. RESEARCH GOVERNANCE, DATA PROTECTION AND SPONSORSHIP

**13.1 Research Governance**

CHaRT is a fully registered Clinical Trials Unit with particular expertise in running multicentre RCTs. The ELECTRIC trial is run under the auspices of CHaRT based at HSRU, University of Aberdeen. This aids compliance with Research Governance and the principles of GCP, and provides support for aspects of trial administration, database support and statistical analyses. The CI ensures, through the TSC and Sponsor, that adequate systems are in place for monitoring the quality of the trial and providing appropriate expedited and routine reports, to a level appropriate to the risk assessment of the trial. The sponsors SOPs are followed and CHaRT SOPs, where appropriate.

**13.2 Data protection**

Data collected during the course of the research is kept strictly confidential and accessed only by members of the trial team, and may be looked at by individuals from the Sponsor organisation or CH sites where it is relevant to the participant taking part in this trial.

Participants are allocated an individual trial number. Participant’s details are stored on a secure database under the guidelines of the 2018 General Data Protection Regulation. The CHaRT senior IT manager (in collaboration with the CI) manages access rights to the data set. We anticipate that anonymised trial data may be shared with other researchers to enable international prospective meta-analyses.

**13.3 Sponsorship**

Glasgow Caledonian University is the sponsor for the trial.

## 14. ETHICS AND REGULATORY APPROVALS

The Yorkshire and The Humber Bradford Leeds Research Ethics Committeein England and the Scotland A Research Ethics Committee have reviewed this trial. The trial is conducted according to the principles of GCP provided by Research Governance Guidelines. Annual progress reports, end of trial declaration, and a final report are submitted to the Sponsor and the individual Research Ethics Committees in England and the Scotland within the timelines defined in the regulations.

**14.1 Protocol compliance and amendment**

The Investigators will conduct the trial in compliance with the protocol given favourable opinion by the Ethics Committee(s). Any amendment to the project is approved by the Sponsors and funder before application to REC, unless in the case of immediate safety measures when the Sponsor is notified as soon as possible. Any deviations from the Protocol will be fully documented using a breach report form.

## 15. QUALITY ASSURANCE

The trial is monitored to ensure that it is being conducted as per protocol, adhering to Research Governance, the principles of GCP, and all other appropriate regulations. The approach to, and extent of, monitoring is specified in the trial monitoring plan and is appropriate to the risk assessment of the trial. The ELECTRIC monitoring plan includes adherence to the Protocol Adherence Checklist which will be assessed during site monitoring visits undertaken by members of the Trial Office. Investigators and their host institutions are required to permit trial related monitoring and audits to take place by the Sponsor and/ or regulatory representatives, providing direct access to source data and documents as requested.

**15.1 Risk assessment**

An independent risk assessment has been carried out by the Sponsor.

## 16. FINANCE AND INSURANCE

The trial is funded by a grant awarded by the NIHR Health Technology Assessment programme (HTA Project: 15/130/73). The necessary trial insurance is provided by Glasgow Caledonian University.

## 17. END OF TRIAL

The end of follow-up for each participant is defined as the final data capture on that individual. The end of the trial is defined as the end of funding. The end of the trial will be reported to the Sponsor and REC within 90 days, or 15 days if the trial is terminated prematurely. If terminated prematurely, the Investigators will inform participants and ensure that the appropriate follow up is arranged for all involved, if appropriate. A summary report of the trial will be provided to the Sponsor and REC within one year of the end of the trial. An end of trial report is also issued to the funders at the end of funding.

## 18. DATA HANDLING, RECORD KEEPING AND ARCHIVING

Clinical data is entered into the database by the designated team members working in each CH site. Questionnaires returned to the trial office are entered there. Staff in the trial office work closely with local PIs and RRAs to ensure that the data are as complete and accurate as possible. Extensive range and consistency checks further enhance the quality of the data. Responsibilities for archiving are documented in the sponsor / site agreement. All essential data and documents (electronic and hard copy) are retained for a period of at least seven years after close of trial according to the funder requirements and relevant Sponsor and CHaRT archiving SOPs. Electronic data will be archived by the University of Aberdeen.

##

